### Recruitment

Interviewers will approach households in 50 clusters of randomly selected Lower Super Output Areas (LSOAs), by knocking on doors from a list of all addresses in the LSOA. Interviewers will recruit one person per household and use a quota target list to ensure selection of sufficient numbers of participants with required characteristics as outlined above to ensure a final representative sample.

An incentive in the form of £10 for completing wave 1 and then £15 for completion of waves 2, 3 and 4 will be offered. Those who are interested in the study will be given a verbal and written explanation by the interviewer.

### Questionnaire design

The first survey will involve collection of demographic and dental history details using standard nationally agreed questions [20]. Participants will then be randomised to different WTP elicitation methods (standard versus incremental). Up to 8 programmes (emerging from initial interviews with the panel (Phase 1, WS1)) will then be described in detail.

For those in the “standard approach” arm, participants will be asked to rank the described programmes in order of preference and then, for each programme, WTP will be elicited initially using a shuffled bidding card method [21] and then an open-ended question asking the participant’s maximum that they are willing to pay in terms of increased taxation. For those in the “incremental” arm, the first task will also be to rank the programmes in order but WTP will then be elicited in terms of the maximum a participant is willing to pay in increased taxation to secure the 8th most preferred programme (i.e. least preferred), followed by respondents being asked to state how much extra in increased taxation they would be WTP for the 7th programme compared to the 8th. Next the extra amount for 6th programme in addition to the value for the 7th and 8th programme will be elicited, then the 5th, etc. For both approaches, where participants give a zero valuation, a separate categorical list of reasons will be given, in order to determine protest and true valuations of zero [22].

Following the first survey, the best method of standard and incremental approaches will be selected by the WS1 panel and used for subsequent surveys. Further programmes (emerging from WS1) will be analysed in three subsequent surveys conducted approximately six-monthly over 2 years, each containing up to 8 programmes.

The questionnaire has been developed specifically for this project (Additional file 2) by the research team with the input of a patient advisory group. The questionnaire was piloted with a small sample of the general public and adjusted accordingly. The scenarios to be valued will be developed as the project progresses with input from the patient advisory group as well as piloting with the general public (these are therefore not available for inclusion in Additional file 1).

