### Intervention: Phase II

The panel will then meet, facilitated by the research team, to tailor the PBMA process. The exact nature of the exercise will depend on the needs of the panel but the general principles will be consistent with the seven steps of micro-PBMA as outlined below [16].Determine the aim and scope of the priority setting exerciseCompile a “programme budget” The current resources used and activity information are identified.Form a “marginal analysis” advisory panelDetermine relevant decision-making criteria and weighting these e.g. maximising benefits, improving access and equity, etc., with reference to specified objectives of the health system and the community.Identify options for (a) service growth (b) resource release from gains in operational efficiency (c) resource release from scaling back or ceasing some servicesEvaluate investments and disinvestments in terms of costs and the criteria established in Step 4 and make recommendations for (a) funding growth areas with new resources (b) moving resources from 5(b) and 5(c) to 5(a).Validate results and reallocate resources

At the point of establishing options to be assessed in marginal analysis (Step 5), as well as continuing on through the ‘normal’ process of weighting criteria and assessing each option against these criteria, the options will be fed into WS2, in which each option will be assessed in terms of the mean societal value expressed as WTP. Once Step 6 is reached by the panel, the results of WS2 will be fed back into the process. WTP values for the programmes will be presented in a variety of ways and the panel will decide on what form of WTP presentation is most useful. The panel will also have to decide how much weight the WTP values will be given in any decisions made.

Phase II will correspond with the ‘Act & Observe’ phase of PAR which involve not only conducting the PBMA as outlined above but also collecting data and reflecting on the application of the framework, focusing on how the panel manage the process devised.

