### Sample

The sample is designed to be representative of the population of England based on gender, age and socio-economic status. Where necessary, results will be weighted to account for differences in demographics of the sample versus the population. For pragmatic reasons, there will be an element of clustering of the sample based on geography.

As the data will be used for econometric modelling, sample size is dictated by the number required for sufficient power for regression models. The Events per Variable approach suggests a minimum of 10 cases per variable to be included in the regression model and with an estimated 15 variables per model and a splitting of the sample in 2 for some analysis (due to the methodological experiment), the minimum number is 300 [19]. In order to ensure a sample of 300 in the final wave, a larger sample will be required at each preceding wave, with previous experience suggesting attrition of 40% after Wave 1 and 15% after each of Waves 2 and 3 meaning an initial sample of 800 would be required. In addition previous experience suggests that certain groups are more likely to drop out so these will be oversampled in the first wave.

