### Survey delivery

The data will be collected via a series of surveys delivered over a 2 year time frame. For Wave 1, the interview will take place face to face using a computer based interface completed by the participant with support from the interviewer. For waves 2–4, the option of online completion will be offered to participants in addition to face-to-face in-home completion as per wave 1.

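### Different programmes are valued in different survey waves by a shrinking panel with a change of mode and no stated common programme, so cross-wave differences in mean WTP mix programme value with wave effects

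*Protocol article*

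**What the plan says.** All references are to the protocol article.

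- **Programmes by wave.** Questionnaire design says of the first survey: "Up to 8 programmes (emerging from initial interviews with the panel (Phase 1, WS1)) will then be described in detail". For the rest: "Further programmes (emerging from WS1) will be analysed in three subsequent surveys", again with a limit of 8 each. Scenarios were still to be developed. No programme is said to appear in more than one wave, and none is barred from doing so.
- **Method.** Wave 1 is randomised between the standard and incremental approaches. After it, "the best method of standard and incremental approaches will be selected by the WS1 panel and used for subsequent surveys".
- **Mode.** Survey delivery describes the first survey thus: "the interview will take place face to face using a computer based interface completed by the participant with support from the interviewer". This changes from the second survey onwards, when "the option of online completion will be offered to participants in addition to face-to-face in-home completion".
- **Respondents.** The Workstream 2 overview targets the same people at each wave. Its Sample section starts from 800, expects attrition of 40%, 15% and 15%, and adds that "certain groups are more likely to drop out so these will be oversampled in the first wave". Weighting is demographic there; Data analysis and the Discussion add weighting for ability to pay.
- **Use.** Intervention: Phase II says "each option will be assessed in terms of the mean societal value expressed as WTP". The results reach the panel at Step 6. The panel chooses how they are presented and how much weight they carry.
- **Time span.** The Workstream 2 overview puts the four waves within 4 months. Questionnaire design has the later surveys about six-monthly over 2 years, and Survey delivery also gives 2 years.

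**The concern.** WTP is collected so that options can be set beside each other when investments and disinvestments are weighed. Two programmes valued in the same wave share respondents, mode, occasion and choice set. Two programmes valued in different waves may share none of these in full. With no common programme, a difference between their means cannot be split into programme value and wave effect.

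The stated safeguards cover part of this. Oversampling and demographic weights act on the groups they are built on, and ability-to-pay weights act on means. None is directed at dropout related to interest in dental services or to WTP itself, and none deals with the change of mode. At stake is whether a programme could look more or less valued because of the wave in which it was placed.

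**Working it through.** **Inputs.** From Sample (Workstream 2): 10 cases per variable, 15 variables, a split in 2, initial sample 800, attrition 40%, 15% and 15%. From Questionnaire design: four surveys of up to 8 programmes.

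**1. The plan's own figures.**
- Minimum sample: 10 × 15 × 2 = 300, which reproduces.
- Retention to wave 4: 0.60 × 0.85 × 0.85 = 0.4335.
- Initial sample needed: 300 / 0.4335 = 692.04, so 693. The stated 800 is not reproduced. It is larger than needed, and this point does not rest on it.

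**2. Expected respondents by wave, from 800.**
- Wave 2: 800 × 0.60 = 480
- Wave 3: 480 × 0.85 = 408
- Wave 4: 408 × 0.85 = 346.8, about 347 (43% of wave 1)

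**3. How many comparisons cross waves.** If every slot holds a different programme there are 4 × 8 = 32 programmes.
- All pairs: 32 × 31 / 2 = 496
- Within-wave pairs: 4 × (8 × 7 / 2) = 112
- Cross-wave pairs: 496 − 112 = 384, or 77%

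**4. What selective dropout alone could do.** The article gives no WTP for leavers, so this is an assumption. Let leavers' mean WTP equal (1 + d) times that of wave-4 stayers. Relative to stayers, the recruited sample's mean is 0.4335 + 0.5665 × (1 + d). The ratio of the unweighted wave-4 mean to the recruited-sample mean is the inverse.

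| d | Recruited mean / stayers' mean | Error in wave-4 mean |
|---|---|---|
| −30% | 0.830 | +20% |
| −20% | 0.887 | +13% |
| −10% | 0.943 | +6% |
| 0 | 1.000 | 0 |
| +10% | 1.057 | −5% |
| +20% | 1.113 | −10% |
| +30% | 1.170 | −15% |

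These are unweighted figures. Planned weighting would remove whatever part runs through demographics or ability to pay.

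**5. Mode, time and choice set.** No figure in the article allows these to be sized. Under the incremental approach, values are built upwards from the least preferred programme, so a value depends on which other programmes share the set and on how many there are. This matters across waves only if that approach is selected.

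**6. Wave-1 method.** With 1:1 allocation (assumed), about 400 of the 800 give wave-1 values by the method later kept.

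**The case against.** - **Silence is not exclusion.** The absence of a repeated programme is read from the word for additional programmes and from silence, in a condensed article whose later scenarios did not yet exist. This stands as a limit: the article does not fix a link, but does not rule one out.
- **The panel design is itself a link.** A reader might infer that nothing ties the waves together. That is not supported. The same people are targeted, so wave-4 respondents would generally also have wave-1 values, and comparison within them removes the change in composition. Selection into that group remains, as do mode, time and choice-set effects.
- **Arms need not be pooled.** A reader might infer that wave-1 values from both methods will be mixed for the panel. Nothing says so, the randomised arms are separable, and using the selected arm alone fits the text.
- **WTP does not decide Step 6.** Options are judged on costs and on the Step 4 criteria. WTP is an added input whose weight the panel sets.
- **Analysis detail belongs elsewhere.** Response weights and mode terms are commonly left to an analysis plan, and the article already mentions sensitivity analysis and possible selection models. So their absence is no fault. The anchor is different: it is a questionnaire decision, and if it is not fielded no analysis can supply it.
- **The wave design has a stated purpose.** It allows many scenarios to be valued and ideas from Workstream 1 to be fed in. That is a fair reason for waves, and an anchor in each leaves it intact.

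**Conclusion.** The point holds for comparisons between waves. Programme, wave and mode change together after wave 1, the panel is expected to fall to 43% of its starting size, and the stated weights address only part of the resulting difference. Comparisons within a wave are unaffected.

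A reader might infer that later programmes will look more valued. The document does not support a direction: leavers could have lower or higher WTP. The range of +20% to −15% at wave 4 rests on an assumed gap of −30% to +30%, takes no credit for weighting, and sets the stayers' mean against that of everyone recruited. It is an illustration, not an estimate. A reader might also take a gap of many months between waves as given. The article states both 4 months and 2 years, and only the longer span makes drift over time a serious component.

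This is an inexpensive improvement worth making before wave 2, not an error that invalidates the survey.

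**What to change.** 1. **Anchor programme.** Repeat one wave-1 programme in each later wave, and report every programme relative to the anchor as well as in pounds. Cost: up to three new-programme slots, leaving 29 distinct programmes instead of 32. Limits: respondents may recall their earlier answer; a single anchor corrects only for effects that act alike on all programmes; and it does not fully remove dependence on the choice set if the incremental approach is selected.
2. **Non-response weights.** Weight waves 2 to 4 using wave-1 WTP (within arm, since the two methods may differ in level), dental history and demographics. All of these are already collected in wave 1, so the cost is analysis time.
3. **Sensitivity analysis.** Repeat cross-wave comparisons within people who complete all waves, with survey mode in the models. About 347 are expected. With 1:1 allocation, about 346.8 / 2 = 173 of them would have wave-1 values by the selected method, if dropout is similar in the two arms.
4. **Wave-1 values.** State that the panel sees wave-1 means from the selected-method arm, about 400 people.
5. **Survey span.** Reconcile the 4 months in the Workstream 2 overview with the 2 years in Questionnaire design and Survey delivery.

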### Survey delivery

The data will be collected via a series of surveys delivered over a 2 year time frame. For Wave 1, the interview will take place face to face using a computer based interface completed by the participant with support from the interviewer. For waves 2–4, the option of online completion will be offered to participants in addition to face-to-face in-home completion as per wave 1.

### Data analysis

As well as appropriate descriptive statistics (weighted where necessary for representativeness and ability to pay), the determinants of WTP will be determined using econometric analysis. The precise modelling will depend on the nature of the data but may include two-part models, tobits and Heckman Selection models. Appropriate sensitivity analysis will be performed.

## Discussion

This study will lead to a development of the PBMA method and an understanding of the use of WTP in PBMA. If the recommendations made in this study are accepted, then there should be a direct improvement in the use of resources in NHS dentistry in England. However, as with any study with a wide scope, there are certain challenges. These challenges are engagement of stakeholders with the PBMA process, reluctance to accept the recommendations by policy makers, the volume of qualitative data gathered and problems associated with the WTP elicitation.

In order to maximise potential engagement, the research team have spent time embedded within stakeholder organisations, especially NHS England and Public Health England working with those who will be approached in recruitment. This has ensured that the project is designed in such a way as to best fit with the organisations and individuals who will need to be involved but has also ensured that a level of trust and understanding has been built between the research team and the stakeholders. In a similar way, this embedding with NHS England, in particular with the key policy makers in the Office of the Chief Dental Officer, has also helped to shape the direction and design of the study to ensure the maximum likelihood of acceptance of the recommendations. Although the policy makers will be kept informed of the study progress in order to maintain interest, the embedding of the research team will be stopped at the beginning of the study and the policy makers will not have any influence on the work of the panel, to ensure an independent, rigorous process is followed.

The volume of data likely to be generated is large and this is part of the reason for choosing the Framework approach to analysis as it is well suited to managing large amounts of data but is also recommended for use where influence on policy is key. In addition, the division of data into 3 phases is an important way of managing the data, allowing analysis to be undertaken within each phase, although overall analysis bringing together findings from across the three themes will be important too.

Finally, the WTP elicitation method has been criticised for being too hypothetical and too vulnerable to bias introduced by the actual elicitation method used as well as ability to pay influencing values [21, 23, 24]. Best practice methods in terms of using a shuffled payment care approach [21], and a cheap talk script [25] or similar appropriate method of reducing hypothetical bias will be used. The use of a tax payment vehicle for a genuine set of services and the use of the values in real life policy decisions will also aid in ensuring hypothetical bias is minimised. Finally, the influence of ability to pay on WTP will be studied and if necessary, weighting will be applied.

## Abbreviations

CDPH: Consultants in Dental Public Health
LDN: Local dental network
NHS: National Health Service
PAR: Participatory action research
PBMA: Programme budgeting marginal analysis
WS1: Workstream 1
WS2: Workstream 2
WTP: Willingness to pay
